### Sample size

HHQ is the primary outcome measure used for the power calculation. The results from a previous study suggest that the mean scores of HHQ for those with mild hearing loss who are seeking help for the first time are expected to be about an average of 26, with a standard deviation of 8 [36]. HHQ has been previously used in a few studies as predictive and outcome measure and shown a shift of around 2.5 to 5 points [11,38]. However, we expect to reduce the mean scores to 22 from 26 after the intervention (that is, reduction in perceived hearing disability by 4 points in HHQ). To detect this effect the sample size was calculated using PASS (NCSS, LLC, Kaysville, UT, USA) power analysis software (two-sample test, two-sided significance level, alpha of 0.05 and beta of 0.8), which showed that 66 participants per group are needed. However, considering the additional 20% loss to follow-up, the required sample size is 158 people in total, with 79 participants assigned to the control group and 79 participants to the intervention group.

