**Methods/Design:**

A randomized controlled trial (RCT) with waiting list control (WLC) design will be used in this study. One hundred and fifty eight participants with self-reported hearing disability (that is, score >20 in the Hearing Handicap Questionnaire (HHQ)) will be recruited to participate in this study. They will be assigned to one of two groups (79 participants in each group): (1) Information and counseling provision using the ‘patient journey’ model; and (2) WLC. They will participate in a 30 day (4 weeks) internet-based counseling program based on the ‘patient journey’ model. Various outcome measures which focuses on hearing disability, depression and anxiety, readiness to change and acceptance of hearing disability will be administered pre (one week before) and post (one week and six months after) intervention to evaluate the effectiveness of counseling.

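### The 20% drop-out allowance multiplies 66 by 1.2 instead of dividing by 0.8, so 79 per group falls about 3 short of 66 at the stated loss; power is also labelled as beta. The effect on power is small.

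*Protocol article*

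**What the plan says.** The Sample size section of the protocol article bases the calculation on the Hearing Handicap Questionnaire (HHQ). First-time help-seekers with mild loss are "expected to be about an average of 26, with a standard deviation of 8", and "we expect to reduce the mean scores to 22 from 26 after the intervention", which is a difference of 4 points. The settings are given as "two-sample test, two-sided significance level, alpha of 0.05 and beta of 0.8", "which showed that 66 participants per group are needed".

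The attrition step follows: "considering the additional 20% loss to follow-up, the required sample size is 158 people in total", split equally into 79 and 79. The Abstract repeats the group size ("They will be assigned to one of two groups (79 participants in each group"), and the recruitment section uses 158 as the number to enrol. The Trial status section reports that recruitment has finished.

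**The concern.** Two statements in this section do not fit its own figures.

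- **Attrition.** A loss rate applies to the people enrolled, not to the people needed at the end. The enrolled number should therefore be the required number divided by the retained fraction. Adding 20% to the required number gives a smaller total, and at the stated loss that total no longer delivers the 66 that the section calls for.
- **Error rate.** Beta is the type II error rate, and power is 1 − beta. A beta of 0.8 cannot go with 66 per group under the stated difference and SD.

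At stake is whether the justification for 158 can be reproduced and whether it delivers what it promises at the attrition it assumes. Others who plan similar trials may copy the calculation.

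**Working it through.** **Inputs**, all from the Sample size section: difference 4 (26 to 22), SD 8, two-sided alpha 0.05, 66 needed per group, 20% loss, 79 per group enrolled. Power is taken as 0.80; step 4 gives the reason.

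**1. The base figure.** The normal approximation is n = 2 × (1.960 + 0.842)² × 8² / 4² = 2 × 7.849 × 4 = 62.8, so 63 per group. The exact two-sample t-test (noncentral t) needs 64. The stated 66 is within 2 of the t-test figure, so the base calculation is consistent with its inputs.

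**2. The plan's inflation, reproduced.**
- 66 × 1.2 = 79.2, taken as 79 per group, and 2 × 79 = 158. This matches the document.
- 66 / 0.8 = 82.5, so 83 per group and 166 in total. This does not match.
- Check on the rounding: 83 × 0.8 = 66.4, which retains 66; 82 × 0.8 = 65.6, which does not.

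**3. What 79 per group delivers.**
- At 20% loss: 79 × 0.8 = 63.2, about 63 per group, or 3 below 66.
- Largest loss that still leaves 66: 1 − 66/79 = 13/79 = 16.5%.

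**4. The beta label.** With a true beta of 0.8 (power 0.20), the same inputs need only about 11 per group. The stated 66 fits power of 0.80 and not power of 0.20, so the label is a slip.

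**5. Effect on power** (difference 4, SD 8, two-sided 0.05, unadjusted comparison). The normal approximation is Φ(4 / (8 × √(2/n)) − 1.960); at n = 63 this is Φ(2.806 − 1.960) = 0.801.

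| Completers per group | t-test | Normal |
|---|---|---|
| 63 (79 enrolled, 20% lost) | 79.5% | 80.1% |
| 66 (the stated need) | 81.4% | 81.9% |

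The loss is about 1.9 percentage points on either basis.

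**6. Planned analysis.** Data collection and analysis specifies analysis of covariance with the baseline score as covariate, which reduces the residual SD to about 8 × √(1 − r²). The document gives no baseline-to-outcome correlation r. If r is assumed to be 0.3, 0.5 or 0.7, 63 per group gives about 83%, 90% or 97% power.

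**The case against.** The strongest reply is that nothing of substance is lost. The plan's inputs need only 63 or 64 per group, so the 63 who remain after 20% loss meet the normal-approximation requirement and miss the t-test requirement by one per group. Adjustment for baseline can raise power further. This stands, and it sets the size of the point.

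Two readings might rescue the arithmetic, but neither does:
- The 20% could mean recruiting 20% more people. The section, however, calls it loss to follow-up. On the other reading the plan covers 16.5% loss, and the wording still needs correction.
- 63 / 0.8 = 78.75 also rounds up to 79. The section, however, gives 66 as the requirement, not 63.

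A reader might also infer more than the document supports:
- *That the trial was planned with 20% power.* The 66 per group in the same sentence rules this out.
- *That the 66 comes from a rank-based test and so conflicts with the planned analysis of covariance.* The section names only a two-sample test. Working back from 66 to a particular procedure is conjecture, and a condensed article need not name the software routine.
- *That the trial is materially underpowered.* The figures for 63 per group do not show this.

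**Conclusion.** The point holds as a minor arithmetic and labelling error. The number enrolled does not retain the stated 66 per group at the stated 20% loss: 79 leaves about 63, where 83 per group (166 in total, 8 more than planned) would have been needed. Beta of 0.8 should read power of 0.80.

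The practical effect is slight, since unadjusted power at 20% loss stays at about 80%. That rests on the section's own difference and SD and on equal loss in the two groups. The gain from covariate adjustment depends on a correlation that the document does not give, so its size is unknown; it would be negligible if baseline and outcome were barely correlated.

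**What to change.** Keep 158, since recruitment is over, and restate the end of the Sample size section along these lines:

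> Power 0.80 (beta 0.20). Enrolling 79 per group retains 66 evaluable participants if loss is at most 16.5%. At 20% loss about 63 per group remain, giving about 79.5% to 80% unadjusted power for a 4-point HHQ difference with SD 8.

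The cost is a few words and a slightly less favourable attrition statement. No participants are added, and neither the design nor the analysis changes. The Abstract's 79 per group can stay, because it correctly gives the number assigned.

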### Blinding

Due to the nature of the study, it is not possible to blind the participants and the clinician. However, the allocation of participants to study groups will be done randomly using computer-generated numbers and with the help of another person (that is, researcher-blinded). However, the participants will be given unique reference numbers to keep the participants’ personal details blinded while analyzing the results.

### Co-intervention and compliance

Considering that the participants do not have any direct contact with the researcher (that is, the trained clinician), co-intervention cannot be avoided. However, participants will be requested not to participate in any interventions which may influence the results during the beginning of the study and will be questioned about this at the end by being asked a similar question after outcome measures have been collected. These notes may help us while analyzing the results. In relation to compliance with the intervention protocol, participants will be encouraged to complete the task after each session throughout this process. A reminder Email will be sent on a regular basis advising the participants about the recommendations made regarding intervention. Moreover, attempts will be made to classify the Email interactions with participants to understand at what phase each participant might be, so that the suggestions and recommendations made will be tailored accordingly.

### Data collection and analysis

Data will be collected via online questionnaires administered through the secure internet-based counseling protocol system one week pre intervention, one week post intervention and six month follow-up. To reduce attrition rate at follow-up, reminders will be sent by Email. However, if the participants decide not to participate further in the study, the reasons for their withdrawal will be recorded. Analysis of covariance will be made for T1 and T2 data with initial T0 measures (that is, pre and post counseling results) as the continuous predictor. Any missing data at T1 and T2 will be imputed with an assumption that values are missing completely at random (MCAR) and using an appropriate imputation method [39].

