### Internet-based audiological rehabilitation

In recent years there has been an increase in the use of the internet for seeking health-related information. Cummings *et al*. suggested that online support groups in the form of a subscription distribution list can help people with hearing loss [24]. Laplante-Lévesque *et al*. used daily internet-based communications (in the form of Emails) in addition to the usual audiological service provided to people with hearing loss [25]. Their study demonstrated that an internet-based counseling program for new hearing aid users could be interactive and effective. Moreover, they found that each participant exhibited different behaviors and shared different thoughts during internet-based audiological counseling. More recently, Thorén *et al*., in a randomized controlled study evaluated the use of a rehabilitative online education program with discussion groups for hearing aid users [12]. They observed significant differences between pre and post counseling sessions in both groups, and the effects were maintained at six months follow-up. Overall, these studies suggest that the internet may be effectively used in audiological rehabilitation.

Considering the increased use of the internet by the general population, which increases flexibility for patients to participate in such programs in their own time and preferred place, and in the interest of reducing clinicians’ contact time, we will employ internet-based counseling in this study.

This paper describes the design of a randomized controlled trial to evaluate the effectiveness of the ‘patient journey’ model in the internet-based pre-fitting counseling of persons with hearing disability.

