### Intervention

Group one will be given ‘patient journey’ counseling which is based on previous studies [7,8,26], through an internet-based counseling protocol system. The focus of this would be on lived experiences of PHD rather than technical information such as the audiogram and hearing aids. This would involve four stages of designated internet sessions and additional tasks which the patients can complete in their own time. This program should be completed within 30 days. These sessions include: Stage 1 - introduction to the concept of the ‘patient journey’ and presenting to the participants a series of questions which may help them to explore their ‘journey’ through hearing loss; Stage 2 - the ‘patient journey’ model of PHI and two case examples will be presented. The PHD will be advised to compare their ‘journey’ to the model presented and identify the similarities and differences; Stage 3 - the ‘communication partners’ journey’ model will be presented and the PHD will be asked to consider how interactions between him/her and the CP may affect various things in the physical, mental and social domains; and Stage 4 - participants will be encouraged to think about how the PHI and CP may influence each other during their ‘journey’ through hearing loss, how they can overcome some of the difficulties they may be experiencing and to think about the potential benefits and the challenges from the audiological management.

Each stage will contain a short video (that is, one to two minutes) which briefly explains the tasks. However, the information presented in the video is also available in text to make sure equal access is provided to those who may find it difficult to understand speech in the video. Having information in different formats (for example, text and video) would help in ensuring that the information is presented in an interactive manner and that it engages the users in the activity. Throughout this process, the participants will be advised to reflect (a simple guide for reflection will be provided) and maintain notes. This reflection exercise is to explore the activity limitations and participation restrictions they have and also to explore the ways in which they can overcome them. In addition, there will be an Email contact with the researcher (who is also a trained audiologist) with whom they can communicate, update their progress with the intervention and seek further assistance.

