The second group, which serves as the WLC, will complete the questionnaire at the beginning of the study and after 30 days will be provided with the same intervention as the other group. During the 30 days waiting period, the WLC will be advised to read generally about hearing loss and its treatment.

The study protocol has been registered in the http://ClinicalTrials.gov Protocol Registration System and the registration number is NCT01611129 (Study ID Number FAS-IT-03).

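### By six months both arms have had the programme, so the T2 ANCOVA compares immediate with delayed treatment and cannot serve as a treated-versus-untreated test of effectiveness

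*Protocol article*

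**What the plan says.** The abstract (Methods/Design) sets out the design: "A randomized controlled trial (RCT) with waiting list control (WLC) design will be used in this study". It says outcomes will be measured before and "post (one week and six months after) intervention to evaluate the effectiveness of counseling".

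Under Intervention, the programme has a fixed length: "This program should be completed within 30 days". The same section says that the waiting-list arm "after 30 days will be provided with the same intervention as the other group".

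Under Data collection and analysis, questionnaires are given "one week pre intervention, one week post intervention and six month follow-up", and the analysis is stated in one sentence for both follow-up times: "Analysis of covariance will be made for T1 and T2 data with initial T0 measures".

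The visible text does not distinguish the T2 analysis from the T1 analysis, limit T2 to description, or acknowledge that the control arm has been treated by then. T0, T1 and T2 are not defined in words. The natural reading is one week before, one week after and six months.

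**The concern.** A waiting-list design has an untreated control only until the waiting arm starts the programme. Here that is day 30. T1 can fall within or close to that window, but T2 cannot. Applying the same model to both times, with effectiveness as the stated purpose of both, invites the T2 result to be read like the T1 result.

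The likely harm is a misread null. If the programme works, works equally well when delayed, and its benefit lasts, the arms should look alike at six months. Read as a treatment-versus-control comparison, that would be reported as an effect that had faded, when the truth is the opposite.

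**Working it through.** **1. Timeline from the stated durations** (day 0 = start of the immediate arm's programme)

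| Event | Day |
|---|---|
| Immediate arm completes | by about 30 |
| Immediate arm T1 (one week after) | about 37 |
| Waiting-list arm treated | about 30 to 60 |
| T2, if six months from start | about 180 |
| T2, if six months from the end of the programme | about 30 + 182 = 212 |

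The waiting-list arm therefore finished 180 − 60 = 120 to 212 − 60 = 152 days before T2. If T2 is instead timed from each arm's own programme, the two arms are equally far from treatment and even less contrast remains.

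**2. The plan's own sample size**

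Inputs from Sample size: a mean HHQ fall from 26 to 22 (4 points), SD 8, two-sided alpha 0.05, and 0.8, which is printed as beta and read here as power. A two-sample t-test needs 63.8, so 64 per group. Dividing the normal-approximation size by the Mann-Whitney efficiency 3/π gives 65.8, so 66. The stated 66 is reproduced closely enough to use. With 66 per arm, t-test power for 4 points is 0.81.

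**3. What the T2 contrast can show**

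Let f be the share of the 4-point effect that the waiting-list arm has gained by T2, with the immediate arm still holding all of it. Then:

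- contrast = 4 × (1 − f)
- standard error = 8 × √(2/66) = 1.39
- power comes from the two-sided t-test with non-centrality contrast / 1.39

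| f (assumed) | Expected contrast | Non-centrality | Power, 66 per arm |
|---|---|---|---|
| 0 (untreated control, for reference) | 4 | 2.87 | 0.81 |
| 25% | 3 | 2.15 | 0.57 |
| 50% | 2 | 1.44 | 0.30 |
| 75% | 1 | 0.72 | 0.11 |
| 100% | 0 | 0 | 0.05 (alpha) |

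The values of f are assumptions; the documents give none. Since both arms receive the same programme, f = 100% is the natural reference case.

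**4. Does baseline adjustment rescue it?**

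ANCOVA reduces the SD to 8 × √(1 − ρ²), where ρ is the baseline-to-follow-up correlation. The documents do not give ρ. With ρ assumed to be 0.5, power for contrasts of 3, 2 and 1 is 0.70, 0.38 and 0.13. With ρ = 0.7 it is 0.85, 0.51 and 0.17. Adjustment sharpens the estimate of whatever contrast exists, but at f = 100% the rejection probability stays at 0.05.

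**5. Why a null is uninformative**

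Suppose the untreated mean would stay at 26. If both arms keep the benefit, the T2 means are 22 and 22, a difference of 0. If both lose it, they are 26 and 26, again a difference of 0. The between-arm test cannot tell these two states apart.

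**The case against.** **The schedule and the contrast are partly inferred.** The analysis sentence does not say that the comparison is between arms, the text gives no waiting-list assessment times after baseline, and the flow chart that may give them is not available. This is fair, but it does not remove the problem. ANCOVA with a baseline covariate in a two-arm randomised trial is naturally a between-arm model. If the waiting-list arm is measured at T2, it has been treated; if it is not, or if T2 is analysed within arms, there is no control at all. On every reading T2 lacks an untreated comparator.

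**The T2 comparison is still randomised.** This stands. A reader might infer that a significant T2 difference would say nothing about effectiveness. That goes too far: if the programme had no effect at any time, the arms would be exchangeable at T2 apart from attrition and the lack of blinding, so a difference would be evidence against no effect. It would concern immediate versus delayed offer and would not measure benefit over no treatment. The weakness is low sensitivity and an ambiguous null.

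**No six-month power was promised.** This also stands. A reader might set the 5% against a planned 80% at T2. The Sample size section, however, powers a reduction after the intervention ("we expect to reduce the mean scores to 22 from 26 after the intervention") and says nothing about six months. The 5% also needs an equal and lasting response in both arms.

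**Two test times.** A reader might further infer an inflated false-positive rate. The article states no rule that success at either time suffices, and alpha allocation is commonly left to the analysis plan, so nothing is claimed on that here.

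**Conclusion.** The point holds in this form: as written, the plan gives the six-month ANCOVA the same role as the T1 ANCOVA, although the control arm has been treated four to five months before T2. The T2 between-arm estimate is the effect of receiving the programme about 30 days sooner.

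Under the protocol's own 4-point effect and SD of 8, its expected value is about 0 if the delayed arm responds equally and the effect lasts. With an assumed 25% to 75% gain in that arm, unadjusted power with 66 per arm runs from 0.57 down to 0.11. A null result at T2 carries no information on whether benefit persists.

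The size rests on the assumed share gained by the waiting-list arm and on the immediate arm keeping its full benefit. The absence of an untreated control at T2 rests only on the stated 30-day crossover. Neither the T1 comparison nor the sample size is called into question.

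**What to change.** Under Data collection and analysis:

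- Name the between-arm ANCOVA of HHQ at T1, adjusted for T0, as the only treated-versus-untreated comparison of effectiveness.
- State that the waiting-list arm's T1 questionnaire is completed before that arm starts the programme. The text does not say so, and it matters because the immediate arm's T1 falls at about day 37 while the waiting-list programme begins at about day 30.
- Label any T2 between-arm ANCOVA as immediate versus delayed treatment. It need not be dropped.
- Describe maintenance as the T1-to-T2 change, with a confidence interval, in the immediate-intervention arm only, and call it uncontrolled. In the waiting-list arm the same interval spans that arm's own treatment, so its change is a before-after effect and not maintenance.

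Bring the abstract's statement of purpose for the six-month measure into line, and limit six-month conclusions to these two descriptions.

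The cost is a change of wording, with no added participants or assessments. The trial gives up a controlled six-month claim of effectiveness, which the design does not support.

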Internet-based rehabilitation programs have recently started coming in to use and studies have shown promising results [11,25]. This internet-based counseling using the ‘patient journey’ model, is expected to benefit the people with perceived hearing difficulties in a number of ways including: reduced perceived hearing disability, decreased anxiety and depression, positive change in the stages of change and increased acceptance of hearing disability. This approach employs narrative-based medicine strategies to positively facilitate people with hearing difficulties. Each PHI may go through very unique experiences of hearing loss [8], however, the ‘patient journey’ model may provide a framework for the typical ‘journey’ of PHI [7], which may help them to focus on key stages while they think about their ‘journey’ through their hearing difficulties. It is important to note that the ‘journey’ may not be as linear in all the cases as is suggested in the typical model; however, we do expect that the participants will go through all of the main phases suggested in the model. Moreover, a recent qualitative study on shared decision-making in rehabilitative audiology emphasizes that PHI ‘wanted rehabilitative audiologists to hear their experiences and preferences and to tailor their interventions accordingly’ [50], which seems to support our approach in this study.

Whilst we expect to reduce perceived hearing disability through this intervention, there are very small chances that the opposite could happen in some cases. This is because thinking about the future challenges related to hearing problems may be overwhelming for some participants. For this reason, care must be taken during this process to boost positive aspects and to reduce negative aspects associated with their hearing problems. However, if proven effective, such a program could be a cost-effective and time-efficient program to help hundreds and thousands of people with perceived hearing difficulties.

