## Abbreviations

ACE: Active communication education; ANOVA: Analysis of variance; CP: Communication partner; HBM: Health belief model; HHQ: Hearing Handicap Questionnaire; HADS: Hospital Anxiety and Depression Scale: HDAQ, Hearing Disability Acceptance Questionnaire; MAR: Missing at random; PHD: Person with hearing disability; PHI: Person with hearing impairment; RCT: Randomized controlled trial; SRMI: Sequential regression multiple imputation; TAQ: Tinnitus Acceptance Questionnaire; URICA: University of Rhode Island change assessment scale; WLC: Waiting list control.

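### Missing T1 and T2 scores are to be imputed assuming MCAR, which is implausible for an open programme-versus-waiting-list trial and would permit imputation that ignores arm and baseline

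*Protocol article*

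**What the plan says.** Under Data collection and analysis, the protocol article fixes the assumption for both post-baseline time points: missing T1 and T2 scores will be "imputed with an assumption that values are missing completely at random (MCAR) and using an appropriate imputation method". The method is described only as appropriate, with a citation. The analysis is covariance-adjusted for baseline: "Analysis of covariance will be made for T1 and T2 data with initial T0 measures" as the continuous predictor. The same section says that if participants withdraw, "the reasons for their withdrawal will be recorded", but no stated analysis uses those reasons.

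The Sample size section plans for attrition, "considering the additional 20% loss to follow-up", as one figure for both arms. The Abbreviations section lists "MAR: Missing at random" and "SRMI: Sequential regression multiple imputation". Neither term appears in the text, and MCAR, which does, is not in the list.

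**The concern.** MCAR is the strongest of the usual missing-data assumptions, and the design gives reasons to doubt it. The Intervention section has one arm complete four online stages and extra tasks within 30 days, while the other waits and is told to read generally about hearing loss. The Blinding section says participants know their arm, and outcomes are self-reported online. The Discussion adds that "thinking about the future challenges related to hearing problems may be overwhelming for some participants". Drop-out that differs by arm and by severity is therefore a realistic prospect, above all at T1.

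The label matters because an imputation method is judged appropriate against the stated assumption. Under MCAR, filling gaps from observed values without regard to arm or baseline HHQ would pass. If drop-out is in fact related to arm and baseline, such filling can create or distort a difference on the primary outcome. MCAR also gives imputation little purpose: if it held, the baseline-adjusted analysis of completers would already be unbiased.

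**Working it through.** **Context figures from the Sample size section.** Difference 4 HHQ points, SD 8, two-sided alpha 0.05, power 0.80 (the stated beta of 0.8 read as power). Normal approximation: n = 2 × (1.960 + 0.842)² × 8² / 4² = 62.8, so 63 per group. The two-sample t-test gives 64, close to the stated 66, at which power is 0.81. Recruitment is 66 × 1.2 = 79.2, taken as 79 per group. A 20% loss means 158 × 0.20 = 31.6, so about 32 participants would need imputed scores.

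**Simulation inputs.**
- From the protocol: 79 per arm, HHQ mean 26 and SD 8, ANCOVA on T0, two-sided 0.05, about 20% missing.
- Assumed, not in the documents: T0–T1 correlation 0.5 or 0.7; normally distributed scores; intervention-arm drop-out with logit(p) = −1.0 + 1.2 × (baseline in SD units); 10% random drop-out in controls (about 21% missing overall); the imputation methods. There were 2,000 simulated trials per scenario.

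**Drop-out dependent on arm and baseline, no true effect** (negative bias falsely favours the programme; ranges cover correlations 0.5 and 0.7):

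| Method | Bias, HHQ points | Type I error |
|---|---|---|
| Within-arm mean, baseline ignored | −1.19 to −1.67 | 0.27 to 0.47 |
| Within-arm single hot deck, baseline ignored | −1.17 to −1.69 | 0.22 to 0.37 |
| Pooled mean, arm and baseline ignored | −0.92 to −1.29 | 0.14 to 0.31 |
| Multiple imputation within arm, using T0 | −0.00 to −0.02 | 0.043 to 0.051 |
| Completers only, ANCOVA on T0 | −0.01 | 0.043 to 0.053 |

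**Analytic check of the first row.** Within-arm mean filling sets the intervention-arm mean to that of its completers, so bias = correlation × 8 × (mean baseline of completers, in SD units). Integrating the assumed drop-out model over a standard normal baseline gives 31% intervention drop-out and a completer mean of −0.298 SD. Then 0.5 × 8 × (−0.298) = −1.19, and 0.7 × 8 × (−0.298) = −1.67. Both match the table.

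**Milder drop-out.** With baseline truncated above 20, correlation 0.7, drop-out of 26% in the intervention arm rising with baseline HHQ and 12% in control (all assumed), pooled-mean filling gave −0.59 points and type I error 0.098. Completers-only ANCOVA gave 0.006 and 0.046.

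The bias across these two patterns is therefore about 0.6 to 1.7 points. Relative to the 4-point target, that is 0.6/4 = 15% to 1.7/4 = 42%.

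**Data truly MCAR, no true effect.** No method was materially biased (at most 0.04 points in size). Multiple imputation held 0.043 to 0.048. Single within-arm filling (mean or hot deck) rejected in 0.089 to 0.109 of trials, because its standard errors are too small.

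**Drop-out dependent on the unseen outcome, no true effect.** Multiple imputation with arm and T0 was itself biased, by −1.36 to −1.81 points, with type I error 0.27 to 0.31. MAR alone does not settle the matter.

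**The case against.** The strongest reply is that the imputation method is not named, and that the only method named anywhere in the document is SRMI. Sequential regression multiple imputation that included arm and T0 would be valid under MAR whatever label the text carries, and the simulated bias would not arise. This stands. The harm comes from the imputation model that MCAR would permit, not from the word alone, and the figures show what could happen rather than what this trial will report.

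Several stronger readings are tempting but not supported:
- A reader might infer that the primary result will be biased by the amounts shown. The documents give neither the method nor drop-out by arm, so the figures are only illustrative.
- A reader might infer that standard errors will be too small. That is a fault of single imputation, and the protocol does not commit to it.
- Pooled-mean filling shrinks a true 4-point effect to 4 × (1 − 0.20) = 3.2 even when data are MCAR. That shows a fault of pooled-mean filling, not of assuming MCAR.
- The Discussion's remark about participants feeling overwhelmed might be read as predicting drop-out. It speaks of very small chances that perceived disability worsens and does not mention withdrawal. It is supporting context only; the unequal demands on the two arms carry the argument.
- The abbreviation list might be read as proof that MAR was intended. ANOVA is also listed and unused, so the list may be a leftover. The mismatch needs an editorial answer but does not show intent.

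The asymmetry between the arms is also clearest at T1. By the six-month T2, controls have been offered the same programme.

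A protocol article may leave the details of an imputation model to an analysis plan. The point here is different: the article states an assumption, and a plan written to it would inherit that assumption.

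**Conclusion.** The concern holds in conditional form. The protocol commits to MCAR, which its own design makes hard to defend and which does not fit the MAR and SRMI entries in its abbreviation list. If drop-out depends on arm and baseline, and the chosen imputation ignores them, the arm difference can be biased and the type I error inflated. The illustrative range is about 0.6 to 1.7 HHQ points and 0.10 to 0.47, against about 0 and 0.05 for multiple imputation using arm and T0. That range rests on assumed correlations of 0.5 to 0.7, assumed drop-out models and assumed imputation methods. Confidence is high that the stated assumption should change and low on the size of any effect in this trial. ANCOVA on T0 is not at fault: applied to completers, it was unbiased when drop-out depended only on arm and baseline.

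**What to change.** - Replace MCAR with MAR for T1 and T2. Nothing is lost if MCAR happens to be true, since MCAR is a special case of MAR.
- Name the method: multiple imputation, for example SRMI, with arm, T0 and the available HHQ, HADS, URICA and HDAQ scores in the model, combined by Rubin's rules. Include programme progress only if it is actually recorded; the article describes participants' own notes and Email updates but no progress variable.
- Reconcile the abbreviation list with the text.
- Add a sensitivity analysis for outcome-dependent drop-out. One option is delta adjustment by arm, with imputed scores of intervention-arm drop-outs made progressively worse until their assumed benefit is gone. The recorded withdrawal reasons can inform its range.

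The cost is revised wording and a little more programming and reporting. The core variables are already scheduled for collection, and sample size and trial conduct are unaffected.
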